## Abstract

**Background:**

School absenteeism (SA) is associated with anxiety, depression, and disruptive behavior. It is a risk factor for academic difficulties and school dropout, which predict problems in adulthood such as social, work-related, and health problems. The main goal of this study is to examine the initial effectiveness of a modular transdiagnostic cognitive behavioral therapy (CBT) intervention (Back2School) for increasing school attendance and decreasing psychological problems, relative to a comparator control arm (treatment as usual [TAU]).

**Methods/design:**

One hundred sixty children, aged 7 to 16 years, will be randomly assigned to either Back2School or TAU. The design is a two (Back2School and TAU) by four (preassessment [T1], postassessment [T2], and 3-month [T3] and 1-year [T4] assessments) mixed between-within design. The primary outcome is school attendance based on daily registration. Secondary outcomes pertain to youth psychosocial functioning, quality of life, bullying, self-efficacy, and teacher-parent collaboration. These secondary outcomes are measured via youth, parent, and teacher reports.

**Discussion:**

This study will provide critically needed empirical evidence on the initial effectiveness of a manualized treatment program for youth with SA. If the intervention is found to be effective, the program can be further implemented and tested in a larger school health effectiveness trial.

**Trial registration:**

ClinicalTrials.gov, NCT03459677. Retrospectively registered on 9 March 2018.

**Electronic supplementary material:**

The online version of this article (10.1186/s13063-018-3124-3) contains supplementary material, which is available to authorized users.

## Background

School is a central context for youth development [1], playing a major role in teaching youth the values of society and preparing them for adult life. Absence from this central context may be precipitated and/or maintained by anxiety, depression, and disruptive behavior [2–4]. School absenteeism (SA) is also a risk factor for academic difficulties and school dropout, all of which are additional predictors of social, work-related, and health problems in adulthood [5–7]. Each day of absence has been shown to have an impact on academic achievement [8]. For Danish schoolchildren, significant negative associations exist between SA on the one hand and school grades, the likelihood of starting secondary education, and the likelihood of completing secondary education on the other hand. Academic and social well-being are significantly lower when there are high rates of SA [9].

In Denmark, the mean rate of SA is 5.6%, amounting to approximately 11 days during a school year [9]. Almost all children are absent from school a few days during a school year owing to illness or other accepted causes, and this level of absence may be considered as nonproblematic and probably without adverse consequences.

Problematic SA has typically been differentiated in three main types: school refusal (SR), truancy (TR), and school withdrawal (SW). SR refers to SA related to emotional distress in the child, where the child does not try to hide absence from their parents, the child does not exhibit severe antisocial behavior, and the parents have made efforts to get their child to school. TR refers to SA related to externalizing problems, where the absence occurs without the permission of the school and the child typically tries to conceal the absence from their parents. SW refers to SA attributable to parental effort to keep the child at home or where there is little or no parental effort to get the child to school [1]. On the basis of their review of the conceptualization of problematic SA and the differentiation of school attendance problems (SAPs), Heyne et al. [1] concluded that although there is an overlap between the occurrence of SR and TR, between 83% and 95% of youth with problematic SA can be reliably classified as displaying SR, TR, or SW.

Interventions for SA have usually been designed for youths presenting with either TR or SR. A systematic review of TR interventions included 5 randomized controlled trials (RCTs) and 11 quasi-experimental design (QED) studies with a total of 1725 students [10]. Interventions aimed at improving school attendance were effective, overall, in reducing school SA with a moderate and significant mean effect size (*g* = 0.46; mean attendance improvement, 4.69 days). However, in 15 of the 16 studies the absence rates were still above 10% following intervention [10]. A recent systematic review of interventions for SR included six RCTs and two QED studies with a total of 425 students [11]. All but one study used a cognitive behavioral therapy (CBT) protocol. There was a moderate and significant mean effect size of attendance (*g* = 0.54). Findings from both reviews were based on a small number of studies and small sample sizes, and there was substantial heterogeneity between studies. Both reviews recommended conducting studies in which randomized controlled designs and larger sample sizes are used.

Most evidence-based treatments (EBTs) are single-disorder treatments and have been criticized for adapting poorly to the more complex and comorbid problems that are often seen in clinical practice [12], as well as in children with problematic SA. Owing to the heterogeneity of problematic SA, more comprehensive intervention approaches that incorporate treatment of both TR and SR are needed [10, 13, 14]. New transdiagnostic CBT interventions using a modular approach have been developed to target anxiety, depression, and behavior problems within the same manual. Weisz et al. conducted a large RCT using a modular CBT program targeting anxiety, depression, and conduct problems and compared it with TAU and standard EBTs. The results showed that the modular approach outperformed the other treatments on most clinical outcome measures [15]. Other transdiagnostic interventions have been developed and have been shown to be feasible for implementation in school settings [16]. In Denmark, a modular transdiagnostic CBT manual for treating anxiety, depression, and behavior problems (Mind My Mind [MMM]) has recently been developed [17] and is being tested in an RCT.

Some children with problematic SA display anxiety and/or depression; some display externalizing problems, some display both, and some display other problems, (e.g., at a family or school level). In addition, negative cognitions concerning the ability to cope with situations associated with school attendance have been shown to be prevalent among children with problematic SA [18, 19]. Self-efficacy concerning school situations has been found to increase following treatment, and treatment that increases self-efficacy may reduce anxiety, depression, and behavior problems and facilitate reengagement with schooling [20].

An intervention that addressed the needs of this very heterogeneous group therefore needs to be based on an initial assessment and case formulation, followed by a modular, transdiagnostic approach that includes evidence-based interventions for anxiety, depression, behavior problems, parent training and teacher training, and a focus on increasing self-efficacy.

The main objective of this study is to test the efficacy of Back2School (B2S) [21], a modular transdiagnostic CBT intervention aimed at increasing school attendance and decreasing anxiety, depression, and behavior problems among youth with problematic SA. The study uses an RCT design with an active control group receiving treatment as usual (TAU). Based on previous studies, our primary hypothesis is that the B2S intervention will be superior to TAU in improving school attendance. Secondary hypotheses are that the B2S intervention will be superior to TAU in reducing anxiety, depression, and behavior problems. We further hypothesize that improvement in school attendance will be mediated by reductions in the youths’ anxiety, depression, and behavior problems and increases in the youths’ and parents’ self-efficacy. Other members of our research team will perform an economic evaluation comparing the B2S group with the TAU group, both in terms of cost utility measured with a quality-of-life measure and in terms of cost benefit measured by subsequent obtained grades, youth education, employment, and income.

## Methods/design

### Study design

The study is a randomized controlled, parallel group, superiority trial that compares TAU with a modular transdiagnostic CBT intervention (B2S) for SA in youths aged 7–16 years. The design is a two (Back2School and TAU) by four (preassessment [T1], postassessment [T2], and 3-month [T3] and 1-year [T4] assessments) mixed between-within design. The overall study design is illustrated in Fig. 1.

**Fig. 1 Fig1:**
[figure not shown]
Flowchart of the Back2School study

### Study setting

The study is a collaboration between Aarhus University and Aarhus Municipality, Denmark. The setting for both the B2S and TAU interventions is within Aarhus Municipality. The B2S intervention is developed and managed by the Center for Psychological Treatment for Children and Adolescents (CEBU) at Aarhus University and conducted at the same place. TAU interventions are conducted by Aarhus Municipality, and they take place at settings such as schools and social services within the municipality.

### Participants, recruitment, and eligibility criteria

Participants will be youth between 7 and 16 years old in primary and lower secondary school with a minimum of 10% parent-reported SA during the last 3 months. Because the study is conducted in collaboration with Aarhus Municipality, participants need to be registered at public schools in Aarhus Municipality. Private schools within Aarhus Municipality register students’ school absence differently from public schools, and they are outside the municipality’s jurisdiction, rendering school absence data unavailable. The study will include all youth from 0 to ninth grade, excluding participants in their second semester of ninth grade. The second semester of ninth grade is the final semester in Danish public schools, and after this semester, Aarhus municipality cannot provide absence data. Because we expect a larger attrition rate in the TAU group for the secondary measures, participants in the TAU group receive a shorter version of the postintervention assessment battery, and families are offered a gift card (value 200 DKK/26 EUR) after the completion of each subsequent assessment.

Participants are self-referred, and the families are required to make initial contact to participate in the study. They may be informed and directed by health or education professionals but cannot be formally referred. Prior to the start of the RCT, the municipality will implement extensive information and media campaigns aimed at families and professionals. Participants can contact project coordinators with questions within office hours via telephone or e-mail. The registration to participate will be through a web-based screening located at the B2S projects web page. The initial screening will be a short questionnaire based on inclusion criteria with the following questions: (1) language and school information, (2) parent-reported school absence regarding their child in the last 3 months (excluding holidays or other legal absence), and (3) contact information for one of the parents.

The study’s inclusion criteria are as follows: (1) enrolled in a public school within Aarhus Municipality; (2) aged 7–16 years and in 0–9th grade (excluding second semester of ninth grade); (3) report more than 10% SA during the last 3 months of school (based on parent-reported information); (4) the youth and at least one of the parents understand and speak Danish sufficiently to participate in treatment and complete questionnaires; (5) at least one of the parents is motivated to work on increasing the youth’s school attendance; (6) commitment to participate in assessment, intervention procedures, and acceptance of random assignment to intervention; and (7) written informed consent provided by the holders of the parental rights and responsibilities.

There are three main reasons for choosing the simple, low-threshold inclusion criteria of 10% absence during the last 3 months. First, the problems of SR and TR do not represent the full spectrum of youth with problematic SA. That is, these two types of absence are not exhaustive [22]. Basing the inclusion criteria on percentage of SA ensures that youth with other types of problematic SA are not excluded. Second, using a low threshold for absenteeism (only 10%) renders the results of the study more relevant to the broader population of youth with SAPs and not only to the smaller group of youth with severe SAPs (e.g., complete absence for the last 6 months). Third, the fact that parents are referring their children to the project for intervention suggests that parents perceive their child’s absence as problematic.

Participants who do not meet one or more of the inclusion criteria will be redirected in the online screening to a web page informing them of why they are not included in the study and where they can seek other help in the municipality. Participants passing the initial screening will receive verbal (by telephone) and written information and will provide informed consent by electronically signing a consent form. Families are informed that participation in the study is voluntary, that their consent can be withdrawn at any time, and that their participation or withdrawal from the study will not affect their access to the municipality’s usual support and treatment. Participating children and their parents will then receive the preintervention assessment battery, and it is required that the child and the parents complete all questionnaires. After completing the assessment battery, participants will be randomized to one of the treatment conditions within a maximum of 4 weeks. If the youth is randomized to participate in the B2S intervention, their main teacher will receive a preintervention assessment battery immediately after the randomization. All children and parents in both conditions, as well as the primary teacher in the B2S condition, will receive a postassessment battery and two follow-up assessment batteries. All assessment batteries are administered electronically.

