### Outcomes

An overview of the included outcome measures and raters (child, parents, and teacher) is presented in Table 2.

**Table 2 Tab2:** Overview of outcome measures, respondents, and assessment points

Measures	Respondent	Time							
		T1		T2		T3		T4	
		B2S	TAU	B2S	TAU	B2S	TAU	B2S	TAU
Primary outcome measure									
School absence: registry	M	●	●	●	●	●	●	●	●
School absence: parent-reported	P	●	●	●	●	●	●	●	●
Secondary outcome measures									
SDQ	Y, P, T	●	●	●	●	●	●	●	●
PECK	Y	●	●	●		●		●	
FAD	Y, P	●	●	●		●		●	
SCAS	Y, P	●	●	●		●		●	
MFQ	Y, P	●	●	●		●		●	
CHU-9D	Y	●	●	●	●	●	●	●	●
SEQ-SS	Y	●	●	●	●	●	●	●	●
SEQ-RSAP	P	●	●	●	●	●	●	●	●
Other measures:									
Background information	P, T	●	●	●	●	●	●	●	●
School and family collaboration	P, T	●	●	●	●	●	●	●	●
ESQ	Y, P, T			●	●				
SRAS-R	Y, P	●	●						

*Abbreviations: B2S* Back2School, *CHU-9D* Child Health Utility 9D Index, *ESQ* Experience of Service Questionnaire, *FAD* Family Assessment Device, *M* Aarhus Municipality, *MFQ* Mood and Feelings Questionnaire, *PECK* Personal Experience Checklist, *P* Parent, *SCAS* Spence Children’s Anxiety Scale, *SDQ* Strength and Difficulties Questionnaire, *SEQ-RSAP* Self-Efficacy Questionnaire for Responding to School Attendance Problems, *SEQ-SS* Self-Efficacy Questionnaire for School Situations, *SRAS-R* School Refusal Assessment Scale–Revised, *T* Teacher, *Y* Youth

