#### Primary study parameters

Mixed linear models (MLMs) will be used to compare groups (B2S and TAU) over time (T1, T2, T3) for all recurrent outcome variables. Later, the same analyses will be performed for the follow-up period (T3, T4). MLMs will be used to measure main effects of group and time and the time × group interaction effects. MLMs tolerate missing values and thus do not unnecessarily compromise statistical power [48]. All MLMs will be estimated with the maximum likelihood method and based on the intention-to-treat sample. All models will include a random intercept, and the slope will be specified as random if improving the model fit evaluated by a significant change in the -2 log-likelihood (- 2LL) fit statistics [49]. A visual inspection of the data and an inspection of the model indices for the time variable will determine the best fit for the time variable. The outcomes of specific problems of relevance in the corresponding subgroups having anxiety, depression symptoms, or behavior problems as their primary problems will be explored.

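### Four of the eight secondary instruments (SCAS, MFQ, PECK, FAD) are not scheduled in TAU after baseline, so the group-by-time comparison planned for them cannot be estimated

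*Protocol article*

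**What the plan says.** All places are in the protocol article.

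- **Participants, recruitment, and eligibility criteria:** larger attrition on the secondary measures is expected in TAU, so "participants in the TAU group receive a shorter version of the postintervention assessment battery".
- **Outcomes, Table 2** ("Overview of outcome measures, respondents, and assessment points"): eight instruments are listed as secondary outcomes. SDQ, CHU-9D, SEQ-SS and SEQ-RSAP have dots in both arms at T1 to T4. PECK, FAD, SCAS and MFQ have dots in both arms at T1, then in B2S only at T2, T3 and T4.
- **Background:** "Secondary hypotheses are that the B2S intervention will be superior to TAU in reducing anxiety, depression, and behavior problems".
- **Primary study parameters, on the choice of model:** "Mixed linear models (MLMs) will be used to compare groups (B2S and TAU) over time (T1, T2, T3) for all recurrent outcome variables". The same analyses follow for T3 and T4, and the time-by-group interaction is among the effects named.
- **Teacher reports (eligibility section again):** "If the youth is randomized to participate in the B2S intervention, their main teacher will receive a preintervention assessment battery", and this happens after allocation. Later: "All children and parents in both conditions, as well as the primary teacher in the B2S condition, will receive a postassessment battery". Table 2 lists a teacher respondent for SDQ, background information, collaboration and ESQ, and these rows have dots under TAU.

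**The concern.** SCAS, MFQ, PECK and FAD all recur over time, so the analysis section covers them. A comparison of change between arms needs some change to be observed in both arms, and in TAU these scales have only a baseline value. What can be reported for them is uncontrolled change within B2S. In a self-referred sample, that change mixes any treatment effect with natural recovery and regression to the mean.

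The risk is practical. If the models are run as described, software that drops aliased terms can return a time effect that is only the B2S pre-post change, and this could then be read as support for the anxiety and depression hypotheses.

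**Working it through.** The plan gives no figure of its own to reproduce here; its sample-size calculation concerns school absence. The check is whether the planned effects can be estimated from the scheduled data.

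**Inputs (Table 2, rows SCAS, MFQ, PECK, FAD)**

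| Arm | T1 | T2 | T3 | T4 |
|---|---|---|---|---|
| B2S | yes | yes | yes | yes |
| TAU | yes | no | no | no |

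**T1–T3, categorical time.** Let G = 1 for B2S and 0 for TAU. The fixed part is

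E(Y) = b0 + b1·G + b2·[T2] + b3·[T3] + b4·G·[T2] + b5·G·[T3],

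which has 6 parameters. The scheduled cells give four equations:

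- TAU, T1: b0
- B2S, T1: b0 + b1
- B2S, T2: b0 + b1 + b2 + b4
- B2S, T3: b0 + b1 + b3 + b5

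The rank is 4 of 6. Only b0 and b1, the baseline mean and the baseline group difference, are individually estimable. The data fix the sums b2 + b4 and b3 + b5, but not the interactions b4 and b5, which are the treatment effects on change.

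**T1–T3, linear time.** E(Y) = b0 + b1·G + b2·t + b3·G·t has 4 parameters. B2S fixes an intercept and a slope, and TAU fixes one point. The rank is 3 of 4, and the slope difference b3 is not estimable.

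**T3–T4.** There are 4 parameters, and both observed cells are in B2S. The rank is 2 of 4. TAU contributes no data, so even a main effect of group cannot be estimated.

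**Comparison.** With every arm-by-time cell filled, as for SDQ, CHU-9D, SEQ-SS and SEQ-RSAP, the ranks are 6 of 6 and 4 of 4.

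**Extent.** Four of eight secondary instruments (4/8 = 50%) are affected. For each, 0 of the 80 planned TAU participants are scheduled for measurement at T2, T3 or T4.

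**What both arms still hold.** Registry and parent-reported attendance, parent SDQ, youth SDQ from age 11, CHU-9D, SEQ-SS, SEQ-RSAP and parent-rated collaboration are held in both arms. The SDQ section lists subscales for emotional symptoms and conduct problems and a total difficulties score. It lists no separate depression score.

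**Teacher reports.** The eligibility text gives teacher batteries to B2S only, the first of them after randomization. Table 2 lists teachers as respondents in rows with TAU dots, but its dots are not split by respondent within arm. A TAU dot in a youth-parent-teacher row could therefore mean youth and parent only. The two places do not settle whether TAU teachers report.

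**The case against.** **The shorter battery is disclosed and has a reason.** It is meant to protect retention in TAU on the shared measures. That stands as a design choice. It does not rescue an analysis statement that was not narrowed to match.

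**Mixed models tolerate missing values, as the plan says.** This does not help here. A whole arm is unmeasured by design after T1, so there are no TAU follow-up values from which to model the missing ones.

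**The empty cells might be an extraction fault.** This is unlikely. The same pattern occurs in four rows, the other secondary-outcome rows are full, and the text on the shorter TAU battery agrees with it.

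**A reader might infer that the secondary conclusions cannot be reached at all.** The documents do not support this. The Background hypotheses name no instrument. Behavior problems can be compared on youth and parent SDQ, and internalizing symptoms on SDQ emotional symptoms. PECK and FAD carry no superiority hypothesis there. What is lost is disorder-specific evidence on anxiety and depression, and the comparison on bullying and family function. For depression, CHU-9D has a sadness dimension in both arms, but it is a utility measure and no substitute for MFQ.

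**A reader might infer that Table 2 flatly contradicts the teacher text.** Because the dots are not split by respondent, this is an ambiguity to reconcile, not a proven contradiction.

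**A reader might infer that the problem-specific subgroups cannot be formed in TAU.** The analysis section does not say how the primary problem is assigned, T1 scores exist in both arms, and the analysis is exploratory. This is not a finding.

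**Conclusion.** The point holds for SCAS, MFQ, PECK and FAD. The time-by-group comparison planned for them cannot be estimated over T1–T3 or T3–T4, whether time is categorical or linear. The superiority hypotheses on anxiety and depression therefore cannot be tested on their dedicated scales. A specific claim for depression has no symptom scale with a separate depression score measured in both arms after T1.

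This rests on reading the empty Table 2 cells as not scheduled, and on reading the reference to all recurrent outcomes as including these four scales. Both are the plain readings.

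It should be fixed, but it does not threaten the trial's main result: attendance is scheduled in both arms at every assessment.

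**What to change.** 1. In Primary study parameters, limit the B2S-versus-TAU models to measures held in both arms after T1.
2. In the Background, restate the secondary hypotheses on SDQ emotional symptoms, conduct problems and total difficulties, parent-rated and, from age 11, youth-rated. Make no specific superiority claim for depression.
3. Label SCAS, MFQ, PECK and FAD after T1 as description within B2S that is not evidence of a treatment effect.
4. Reconcile the teacher text in the eligibility section with the Table 2 rows that name a teacher, stating for each arm whether teachers report. If the eligibility text governs, treat teacher reports as non-comparative. For children under 11, the parent is then the only SDQ rater common to both arms.

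The cost is wording, plus weaker and less disorder-specific secondary claims. No sample-size figure changes.

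Adding scales to the TAU battery is not proposed. Trial status dates the start of inclusion to September 2017 and this version to October 2018, so families already past T2 could not be recovered. A longer battery would also work against the stated attrition rationale.
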